## 2.3 Potential Risks and Benefits

### 2.3.1 Potential Risks

This study uses two types of anti-malarial drugs to remove blood and liver stages of malarial infections in the study children. A 3 day course of Coartem (artemeter-lumefantrine (AL)) will be used to clear blood stages in both pre-treatment arms while primaquine (PQ) will be used to eradicate liver stages in the pre-erythrocytic pre-treatment arm. In addition, a 3-day course of chloroquine will be administered to all study children at the beginning of drug treatment to assist with the clearance of blood-stages and achieve effective clearance of hypnozoites, together with primaquine, in the pre-erythrocytic arm. AL and chloroquine are well tolerated in PNG children and the schedule and dosage used in the trial correspond to the national standard treatment guidelines. Primaquine has been extensively used in the past in PNG as a gametocidal drug as well as in a short course for eradication of *P. vivax* liver stages but is rarely used today. Primaquine is generally well tolerated and has been used for the eradication of *P. vivax* liver stages in children as young as 3 months in trials of mass drug administration for the eradication of malaria in Vanuatu (13). In addition, in the recent cohort conducted in Ilaaita 150 children 1-5 years were treated with 14 days of primaquine. Detailed monitoring of side effects revealed that drug was safe and very well tolerated ([name] et al in prep). As the drug may lead to gastro-intestinal side effects (nausea etc) if not taken with food, we will give the drug with a bit of soft food prior to drug administration and actively monitor side effects during the entire duration of treatment. The use of primaquine is contraindicated in people with G-6-PD deficiency where treatment with 8-aminoquinolines may induce hemolytic anaemia. We will therefore screen all eligible study children for the presence of G-6-PD deficiency and children with less than 60% G-6-PD activity will be excluded from the study. Children with mild G-6-PD deficiency (60-80% activity) will be randomized to the two arms of the study.

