### **2.3.2 Known Potential Benefits**

The present study has potential direct benefits for the study participants and general benefits for populations in malaria endemic areas in the Southwest Pacific, Southeast Asia and South America.

For participants a potential benefit is the intensive clinical follow-up resulting in earlier diagnosis and treatment of malaria and other common childhood illnesses. In addition, children with G-6-PD deficient will be diagnosed and then counseled in regards to what drug or food the children should avoid.

For PNG and the wider scientific community the study will provide an in-depth assessment of the burden of malarial infection and disease in childhood in PNG and thereby assist in improving diagnosis and treatment. In particular, the determination of the contribution of long lasting liver stages to the burden of *P. vivax* infections and episodes will assist in re-assessing the potential use of liver stage eradication in the national antimalarial treatment guidelines and in future attempts at local malarial elimination. The close monitoring of the PQ treatment will provide important safety and efficacy data on the use of Primaquine for liver stage eradication in children 5-10 years, while the G-6-PD testing will provide data on the prevalence and severity of G-6-PD deficiency in lowland PNG.

Last but not least, the study will contribute to the development of malaria vaccines and interventions by providing an in-depth assessment of naturally acquired immunity to *P. falciparum* and *P. vivax*. The knowledge thus gained will assist in accelerating field testing of existing vaccine candidates.

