## 4 STUDY DESIGN

In this study 500-600 children aged 5-10 years will be screened, enrolled and randomized to 2 arms of a longitudinal cohort study. The randomized arms will comprise:

- 250-300 children pre-treated with 3 days Chloroquine (CQ), 4 weeks Primaquine (PQ) and 3 days Coartem (CO)
- 250-300 children pre-treated with 3 days Chloroquine (CQ), 4 weeks Placebo (PL) and 3 days Coartem (CO)

At enrolment all eligible children aged 5-10 years in the study area will be screened for Glucose-6-Phosphate Dehydrogenase deficiency (G-6-PD) and the presence of severe anaemia or malnutrition. Children with less than 60% G-6-PD activity, haemoglobin <5g/dl or severe malnutrition (weight-for-age nutritional Z score [WAZ] <60th percentile) will be excluded from the study. All other children will be randomized to the two treatment arms of the study.

Drug treatment will commence at enrolment. All children will receive CQ on days 1-3. Children will also receive either PQ (0.5 mg/kg) or placebo on days 1-5, 8-12, 15-19 and 22-26 (i.e. Monday to Friday for 4 weeks). During the third week of drug treatment all children will receive CO on days 15-17 (according to national treatment guidelines). Children will be actively monitored for side effects including measurement of haemoglobin levels at days 1, 8, 15 and 22.

Following completion of treatment, children will undergo a clinical examination and a 10 mL venous blood sample will be collected on day 29 (i.e. 26 days after their last dose of CQ, 12 days after their last dose of CO and 3 days after their last dose of PQ or PL).

Subsequently, all enrolled children will be followed using 2-weekly active and continuous passive case detection at a local health centre for 8 months (Week 2-32). Active follow-up consists of morbidity surveillance visits to monitor clinical malaria illness not reported to a health facility, as well as blood sampling for the detection of asymptomatic malaria. These visits will include collection of a medical history of the preceding 2 weeks to determine incidence of malarial infections and bed net usage, a physical examination, measurement of axillary temperature. A 250µl finger prick blood sample will be collected every 2 weeks for the first 12 weeks and 4 weekly thereafter, i.e. weeks 2, 4, 6, 8, 10, 12, 16, 20, 24, 28 and 32.

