### **6.1.4 Drug Treatment**

Drug treatment will at enrolment. All children will receive a course of course of Directly Observed Treatment (DOT) with CQ on days 1-3. Depending on the treatment arm children have been randomized to, they will also receive DOT of either PQ (0.5 mg/kg) or placebo(PL) on days 1-5, 8-12, 15-19 and 22-26 (i.e. Monday to Friday for 4 weeks). The use of placebo (PL) allows both the participants and study teams to be blinded to the treatments arms. During the third week of drug treatment all children will receive Coartem on days 15-17. All drug treatments will be given with food and observed by the study team. If children do not swallow the drugs properly or vomit them within 30 minutes of administration another dose will be administered.

In order for all children to complete treatment at the same time, the following schedule will be implemented for both rounds of drug treatment:

- Week 1: Commence CQ/PQ and CQ/PL treatment regime
- Week 2: Continue PQ and PL treatment regime
- Week 3: Commence Coartem/PQ and Coartem/PL treatment regime
- Week 4: Continue PQ and PL treatment regime

Treatment side effects will be monitored by study staff at DOT treatment time points. Hemoglobin will be measured at regular intervals during the treatment period to assure that no children are undergoing a hemolytic reaction to primaquine. Children that show adverse reactions to chloroquine, primaquine or Coartem will be excluded from further pre-treatment and subsequent participation in the study. Parents and/or guardians of study participants will be encouraged to seek

medical care for their children, to report any symptoms of malaria, fever, or illness at the earliest opportunity, and to report any anti-malarial treatments received or used. Parents and/or guardians of study participants will be encouraged to seek medical attention immediately if their child has any sign or symptoms of illness or any other condition that they deem as a threat to their child's well-being. They will be advised of their rights to withdraw from the study at anytime should they wish to do so and no medical care or treatment will be refused by the PNGIMR field staff as a form of penalty.

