### **9.1 Definition of Adverse Event (AE)**

Adverse events that may occur from study related activities, such as pre-treatment with chloroquine, artesunate and primaquine, the drawing of blood (an overly deep finger-stick or infection or cellulitis at the site of the finger-stick or venipuncture). Only study related AEs will be reported in an annual report to the IRB.

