### **9.3 Reporting Procedures**

All SAEs will be reported to the PNG IMR IRB within 3 working days. Adverse events will be reported annually in summary fashion.

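### Section 9.1 restricts non-serious adverse events to study-related ones, and no side-effect or haemoglobin outcome is named, although primaquine safety data are promised

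*Protocol*

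**What the plan says.** **The promise.** Protocol Section 2.3.2 lists among the benefits: "The close monitoring of the PQ treatment will provide important safety and efficacy data on the use of Primaquine for liver stage eradication".

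**The collection.** Section 4 states: "Children will be actively monitored for side effects including measurement of haemoglobin levels at days 1, 8, 15 and 22". Section 6.1.4 adds: "Treatment side effects will be monitored by study staff at DOT treatment time points". Neither sentence limits recording to events thought to be related. Section 4 counts 20 contacts for supervised dosing and plans 250 to 300 children per arm. Section 6.1.4 says the placebo keeps participants and study teams blinded. On who is exposed, Section 2.3.1 says: "Children with mild G-6-PD deficiency (60-80% activity) will be randomized to the two arms of the study".

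**The adverse event rule.** Section 9.1 describes: "Adverse events that may occur from study related activities, such as pre-treatment with chloroquine, artesunate and primaquine, the drawing of blood". It continues: "Only study related AEs will be reported in an annual report to the IRB". Section 9.3 adds: "Adverse events will be reported annually in summary fashion". Neither section mentions treatment arm.

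**Serious events.** Section 9.3 sends all serious adverse events to the IRB within 3 working days, and Section 9.3.1 requires them to be reported whether or not they are thought related.

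**The outcomes.** Sections 8.1.1 and 8.1.2 list malaria infections and clinical episodes only. Sections 11.1 and 11.3 follow the same list. No side-effect or Hb outcome appears.

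**The concern.** Relatedness is part of the definition of an adverse event here, as well as a filter on one report. A non-serious event judged unrelated is arguably not an adverse event under Section 9.1 at all. That judgement is hard to make in this trial. The study teams are blinded, every child receives chloroquine and Coartem, and malaria itself causes fever, gastro-intestinal symptoms and low Hb. The protocol does not say who judges relatedness for non-serious events.

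A randomised placebo arm makes individual attribution unnecessary. The difference in all events between the arms estimates the effect of primaquine without anyone deciding what caused a given episode of nausea or a given fall in Hb. The protocol collects what that comparison needs but does not name it as an outcome.

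At stake is a modest excess of gastro-intestinal symptoms or mild haemolysis. Section 2.3.1 recognises both as primaquine risks, and the trial includes children with reduced G-6-PD activity. For non-serious events, the annual summary is the only reporting route that Section 9 specifies.

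**Working it through.** The protocol states no safety figure, so there is none to reproduce. The check has two parts: what the randomised comparison would give, and what a relatedness filter does to it.

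**Inputs.** From Section 4: n = 250 to 300 per arm. Assumed, because the protocol gives none: Hb SD of 1.0 to 1.5 g/dL, background symptom frequency b = 10%, two-sided alpha of 0.05.

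**1. Precision of the arm comparison (95% half-width)**

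- Hb, n = 250: 1.96 × SD × √(2/250) = 0.175 g/dL (SD 1.0) to 0.263 g/dL (SD 1.5).
- Hb, n = 300: 1.96 × SD × √(2/300) = 0.160 to 0.240 g/dL.
- Symptom at 10%, n = 250: 1.96 × √(2 × 0.10 × 0.90/250) = 0.053, or 5.3 percentage points.
- Symptom at 10%, n = 300: 1.96 × √(2 × 0.10 × 0.90/300) = 0.048, or 4.8 points.

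At 80% power, the detectable Hb difference with 250 per arm is (1.96 + 0.84) × √(2/250) = 0.25 SD. The detectable symptom contrast is about 10% against 18.8% with 250 per arm, or 10% against 18.0% with 300.

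By contrast, zero attributed events among 250 primaquine children gives a 95% upper limit of 1 − 0.05^(1/250) = 1.2%. That bounds the attributed rate only and says nothing about events judged unrelated.

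**2. Effect of a relatedness filter**

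Let e be the true excess on primaquine, s the share of drug-caused events that staff call related, and f the share of background events they call related. Take s and f as unaffected by arm, as blinding would encourage. Then:

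- rate kept on placebo = f × b
- rate kept on primaquine = f × b + s × e
- difference seen = s × e

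Power = Φ[(|p1 − p0| − 1.96 × SE0)/SE1], with SE0 = √(2p̄(1 − p̄)/n) and SE1 = √((p0(1 − p0) + p1(1 − p1))/n). With b = 10%, e = 8 points (assumed) and n = 250:

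| Events counted | Placebo | Primaquine | Difference | Power |
|---|---|---|---|---|
| All events | 10% | 18% | 8 points | 73% |
| s = 100%, f = 10% | 1% | 9% | 8 points | 99% |
| s = 70%, f = 50% | 5% | 10.6% | 5.6 points | 65% |
| s = 40%, f = 50% | 5% | 8.2% | 3.2 points | 30% |

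Two things follow. Under these assumptions the difference seen is understated by the factor s whenever s is below 100%, however well blinded the judgement is. Power can go either way: a very accurate filter removes noise and helps, and a poor one discards much of the effect. The protocol gives no basis for placing s or f. Counting all events removes the dependence on both.

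**The case against.** A reader might infer three stronger things, and the protocol supports none of them.

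- **That the trial cannot deliver primaquine safety data.** The restrictive sentence governs the annual report to the IRB. It does not limit what is recorded, analysed or published. Side effects and Hb are monitored in both blinded arms under Sections 4 and 6.1.4, and the Hb part of the fix uses data already collected.
- **That the safety report would have no comparator.** Attributed events on placebo are still a comparator, and blinding limits differential attribution. Section 2 of the working shows that a filter can even raise power.
- **That serious haemolysis could be filtered out.** Any event meeting the serious definition, including hospitalisation or another important medical event, is reported whatever its cause.

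It is also fair to say that safety is not among the stated aims or objectives, and that table layouts and the model for Hb commonly belong in an SAP, which is not shown. Their absence from the protocol is no fault.

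All of this stands, and it limits the point. It does not answer two things that the protocol itself fixes: a definition of adverse event with relatedness inside it, and an outcome list that omits what Section 2.3.2 promises. Both are normally protocol content.

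**Conclusion.** The point holds in a limited form. The design can yield randomised primaquine safety data. The protocol filters non-serious events by relatedness in Section 9.1 and does not name the arm comparison of side effects and Hb as an outcome. No primary or secondary malaria conclusion is affected.

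The size cannot be fixed from the document. The unfiltered comparison with 250 per arm would be informative, with half-widths of roughly 0.18 to 0.26 g/dL for Hb and 5.3 points for a symptom at 10%, given the assumed SD and background frequency. Under the illustrative 8-point excess, filtering moves power from 73% to anywhere between 30% and 99%, depending on attribution accuracy that nobody can state in advance. For the band with 60 to 80% G-6-PD activity, the protocol gives no number of children, so no precision can be claimed.

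The change is worth making because it is cheap and removes reliance on an unverifiable judgement.

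**What to change.** - **Section 9.1:** define and record non-serious adverse events in the treatment period regardless of cause, with relatedness as a separate field. The related-only annual report can still be drawn from that field.
- **Section 8.1.2:** add safety outcomes summarised by randomised arm, namely the proportion of children with each side effect, and Hb change from day 1 to each of days 8, 15 and 22. Adjustment for day-1 Hb and table layout can be left to the SAP.
- **Same section:** add a descriptive display for children with 60 to 80% G-6-PD activity, stating their number and making no claim of power.
- **While editing 9.1:** it names artesunate among the pre-treatment drugs, whereas Sections 4 and 6.1.4 name Coartem. These passages should be reconciled.

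The cost is slightly more adverse event recording over the four weeks of observed dosing and a few extra tables. No new visit or blood sample is needed.

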### **9.2 Definition of Serious Adverse Event**

A serious adverse event (SAE) includes any untoward medical occurrence that:

- Results in death during the study period;
- Is life threatening (defined as a subject at immediate risk of death at the time of the event);
- Requires in-patient hospitalization or prolongation of existing hospitalization;
- Results in persistent or significant disability or incapacity or required intervention to prevent permanent impairment or damage;
- Any other important medical event that may not result in death, be life threatening, or require hospitalization may be considered an SAE when, based upon appropriate medical judgment, the event may jeopardize the subject and may require medical or surgical intervention to prevent 1 of the outcomes listed above.

### **9.3 Reporting Procedures**

All SAEs will be reported to the PNG IMR IRB within 3 working days. Adverse events will be reported annually in summary fashion.

### **9.3.1 Serious Adverse Event Detection and Reporting**

Severe adverse events may be detected either at the 2-week regular health check or at any time during passive morbidity surveillance at Albinama Health Center or surrounding Aid Posts. Staff will be trained to recognize SAEs and will be instructed to report them immediately to the study coordinator or the health center based IMR nurse. In addition, parents and/or guardians of participants will be encouraged to report any serious medical problems of their child to the study team as quickly as possible.

For all events meeting the above described definition of Serious Adverse Events, the completion of the PNGIMR Serious Adverse Event report form is required.

The SAE Form will be reviewed by the study physician, who may request additional information or carry out further investigations.

The study clinician will complete an SAE Report Form within the following timelines:

All deaths and life-threatening events, whether related or unrelated, will be recorded on the SAE Report Form and sent by fax within 24 hours of site awareness of the death or life-threatening event to the study clinician and principal investigators.

Serious adverse events, other than death and life-threatening events, and regardless of the relationship, will be reported via fax by the site within 72 hours of site awareness of the event.

### **9.3.2 Type and Duration of the Follow-up of Subjects after Adverse Events**

All SAEs/AEs will be followed until satisfactory resolution or until the Study Clinician deems the event to be chronic or the patient to be stable.

## **9.4 Halting Rules**

The sponsor and/or IRB can however stop the study at any time, if there are overriding concerns for the safety of study participants.

## **10 CLINICAL MONITORING STRUCTURE**

As a self-sponsored study, no external monitoring of study activities will be preformed. In order to assure the safety of participants and integrity of study databases, the study will however follow Good Clinical Practice and quality assurance guidelines as outlines the IMR GCP – guidelines.

The study investigators are committed to providing access to the standard level of care (ie, therapy with approved agents according to the guidelines of the PNG Ministry of Health and the World Health Organization [WHO]) for participants. Children with illnesses that cannot be treated by field clinics will be referred the Albinama Health Center or Maprik Hospital where they will be treated according to PNG standard treatment guidelines.

## 11 STATISTICAL CONSIDERATIONS

The analyses of this study will follow standard approaches for cohort studies. Time-to-event outcomes will be analysed using survival analysis, incidence rates by Poisson regression.

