**Secondary Objectives:**

- Determine the contribution of long-lasting liver-stages to risk of infection with *P. ovale*.
- Determine the contribution of long-lasting liver-stages to risk of clinical disease with *P. vivax* and *P. ovale* in semi-immune children.
- Investigate the relationship between presence of asexual and sexual stage *P. vivax* and *P. falciparum* parasites following radical cure.
- Assess the effect of cumulative prior exposure to malaria on risk of acquiring new malarial infection and risk of developing clinical illness

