## **11.2 Sample Size Considerations**

### **11.2.1 Primary Outcome Measures**

No estimates for time to first *P. vivax* infection are available for the study community however, in the above-mentioned treatment time-to-reinfection study in children 6-12 years of age in neighbouring Madang province the median time re-infection was 54 and 118 days for PCR and light microscopically detected *P. vivax* infections, respectively. Assuming a 50% decrease in time to first new *P. vivax* infections following LLIN distribution then a sample size of 200 children per arm be sufficient to find a reduction of 30% (hazard ratio 0.70) and 34% (hazard ratio 0.66) of PCR and LM-detectable *P. vivax* infections in the CQ/PQ/CO compared to the CQ/PL/CO group with a power of 90%. This sample size was increase by 25% to account for loss of follow-up and by 5% for children that receive less than 14 days of directly observed primaquine treatment/

In a recently completed cohort study in this region, the incidence of clinical *P. falciparum* malaria in children aged 1-3 years was estimated at 2.6 episodes per child per year (any density). Although no estimates for the incidence of clinical *P. falciparum* malaria in children aged 5-10 years in this region, in a recent treatment time-to-reinfection study in children 6-12 years of age in neighbouring Madang province, the incidence was estimated at 1.7 episodes per child per year (any density). The recent distribution of long-lasting insecticide treated bednet (LLIN) will have reduced this incidence by 60%.

Thus, assuming an incidence of 0.5 episode of *P. falciparum* per child per year (any density in this cohort of similarly aged children, a sample size of 500 children will thus be sufficient to detect 20% decrease in incidence between the two treatment arms with a power of 90%.

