## 11.3 Analysis Plan

### 11.3.1 Primary Outcome Measures

#### 11.3.1.1 Incidence of clinical *P. falciparum* episodes during follow-up

This is a primary objective of the study and will be evaluated by assessing differences in the risk of *P. falciparum* clinical malaria with in both treatment arms.

The analysis strategy for these outcomes is centered on different variations of Poisson regression. The outcome variables are total number of *P. falciparum* episodes (over 32 weeks of follow-up) and incidence of 1st or only episode. Exposure will be defined as the total risk time per child as outlined above. Analyses will be adjusted for possible covariates including infection status at baseline, sex, age, host genetic traits, and nutritional state of child.

The analyses will be done both for episodes defined as axillary temperature  $\geq 37.5^{\circ}\text{C}$  plus any parasitemia or axillary temperature  $\geq 37.5^{\circ}\text{C}$  plus *P. falciparum*  $> 5000/\mu\text{L}$ .

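### Poisson regression is named for total clinical episodes per child with no allowance for overdispersion, so intervals would be too narrow if children differ in risk beyond the offset and covariates

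*Protocol*

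**What the plan says.** The opening of section 11 gives the general rule: "Time-to-event outcomes will be analysed using survival analysis, incidence rates by Poisson regression".

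Section 11.3.1.1 is more specific for clinical episodes: "The analysis strategy for these outcomes is centered on different variations of Poisson regression". It then defines what is modelled: "The outcome variables are total number of *P. falciparum* episodes (over 32 weeks of follow-up) and incidence of 1 st or only episode". The offset is each child's own time at risk: "Exposure will be defined as the total risk time per child as outlined above". The covariates are also given: "Analyses will be adjusted for possible covariates including infection status at baseline, sex, age, host genetic traits, and nutritional state of child".

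Sections 8.1.1 and 11.1.2.1 make the incidence of clinical *P. falciparum* and *P. vivax* episodes a primary outcome. Section 11.3.2 carries the same approach over to the remaining outcomes, including *P. malariae* and *P. ovale*. No section mentions overdispersion, negative binomial regression, robust standard errors or random effects, and no section states an alpha.

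**The concern.** A child can contribute several episodes, so the outcome is a count. Poisson regression takes its standard error from the assumption that the variance equals the mean, given the offset and covariates. If children still differ in risk after that, the counts vary more than the model allows. The standard error is then too small and the test rejects too often when there is no treatment effect.

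The protocol gives reasons to expect such differences. A primary objective of Aim 2 is to relate immune responses to later infection and disease, yet immune response is not among the listed covariates. A secondary objective reads: "Assess the effect of cumulative prior exposure to malaria on risk of acquiring new malarial infection and risk of developing clinical illness". Exposure enters the covariate list only indirectly, through age and baseline infection. Bed net use is recorded at baseline and at every follow-up visit (sections 6.1.5 and 6.1.6) but is not listed either.

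At stake is a primary comparison: a chance imbalance in a few high-risk children could be reported, with misleading precision, as an effect of liver-stage clearance on clinical malaria.

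**Working it through.** **Inputs from the protocol.**
- Planning incidence, section 11.2.1: "Thus, assuming an incidence of 0.5 episode of" *P. falciparum* per child-year.
- The same section cites 1.7 per child-year from a neighbouring province and a 60% reduction from bed nets. That gives 1.7 × 0.4 = 0.68, not 0.5, so both rates are carried through.
- Follow-up is 32 weeks. There are 250 to 300 children per arm (section 4); 250 is used.

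**Inputs assumed.** Nominal two-sided alpha of 5%. Child-level risk, after offset and covariates, follows a gamma distribution with mean 1 and variance k. The documents give no k, so a range of 0.5 to 3 is shown.

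**The plan's own figure.** The only figure tied to this comparison is 90% power for a 20% decrease. With 250 per arm, the expected events are 250 × 0.5 × 32/52 = 76.9 and 0.8 × 76.9 = 61.5. The plain Poisson standard error of the log rate ratio is √(1/76.9 + 1/61.5) = 0.171. Then |ln 0.8|/0.171 = 1.305, and power = Φ(1.305 − 1.96) = 26%. The 90% is therefore not reproduced. That is a separate matter, and nothing below depends on it.

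**Variance inflation.** Mean episodes per child: m = rate × 32/52, which is 0.308 at 0.5 and 0.418 at 0.68 per child-year. Under gamma-Poisson counts, variance/mean is φ = 1 + k·m.

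**False-positive rate of plain Poisson.** α = 2·[1 − Φ(1.96/√φ)]. Example at 0.5 per child-year with k = 1: φ = 1.308, √φ = 1.144, 1.96/1.144 = 1.714, α = 8.7%.

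The formula was compared with 10,000 simulated no-effect trials per setting (unadjusted, full follow-up):

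| Rate per child-year | k | φ | Poisson, formula | Poisson, simulated | Robust SE, simulated |
|---|---|---|---|---|---|
| 0.5 | 0.5 | 1.154 | 6.8% | 6.7% | 5.1% |
| 0.5 | 1 | 1.308 | 8.7% | 8.3% | 5.1% |
| 0.5 | 1.5 | 1.462 | 10.5% | 10.6% | 5.4% |
| 0.5 | 2 | 1.615 | 12.3% | 11.8% | 4.9% |
| 0.5 | 3 | 1.923 | 15.8% | 15.6% | 5.4% |
| 0.68 | 0.5 | 1.209 | 7.5% | 7.7% | 5.4% |
| 0.68 | 1 | 1.418 | 10.0% | 9.3% | 4.8% |
| 0.68 | 2 | 1.837 | 14.8% | 14.8% | 5.2% |
| 0.68 | 3 | 2.255 | 19.2% | 18.7% | 5.3% |

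**Where 10% is reached.** φ must be (1.96/1.645)² = 1.42. So k = 0.42/0.308 = 1.36 at 0.5 per child-year, and 0.42/0.418 = 1.00 at 0.68.

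**Interval width.** On the log scale the correct interval is √φ times the Poisson one. At 0.5 per child-year that is √1.154 = 1.07 for k = 0.5 and √1.923 = 1.39 for k = 3.

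**Scope.** First-or-only and time-to-first outcomes allow at most one event per child, so repeat events in high-risk children cannot inflate their variance.

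**The case against.** The strongest reply is that plain Poisson is not fixed. Section 11.3.1.1 speaks of variants in the plural, and negative binomial or robust-variance Poisson can fairly be counted among them. Which variant is used is often settled in a statistical analysis plan, and one may exist. This stands in part: a reader should not conclude that the protocol rules out a valid analysis. But section 11 is unqualified and no variant is named, so an analysis that follows the text literally uses model-based standard errors. The wording also leaves open which variant supplies the primary p-value.

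A reader might also infer that the model treats every child as having the same risk. It does not. Risk may differ through time at risk, age, sex, baseline infection, host genetics and nutrition, and the covariate list is open-ended. Only residual variation matters. The simulations are unadjusted, so k must be read as what remains after adjustment.

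A third tempting reading is that the false-positive rate is at least double the nominal level. The protocol's figures do not show this. Counts are low, and at the planning rate k of 0.5 to 1 gives about 7% to 9%. Larger inflation can be calculated at 1.7 episodes per child-year, but section 11.2.1 says bed nets have since reduced that rate, so it should not be used to size the problem.

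**Conclusion.** The point holds as a conditional weakness in a named method. If children differ in risk beyond the offset and covariates, as the protocol's aims lead one to expect, model-based Poisson intervals for the total-episode rate ratio are too narrow. At the planning rate the false-positive rate would be about 7% to 16%. This rests on an assumed two-sided 5% level, 250 children per arm, gamma-distributed risk and an assumed residual variance between 0.5 and 3. A doubling to 10% is possible but not established.

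The concern covers total episode counts only. It would be wrong to extend it to all the primary outcomes in section 8.1.1. For a given k the inflation shrinks with the mean count, so it matters less for the scarce species and for the high-density case definition.

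**What to change.** In sections 11 and 11.3.1.1, state that total *P. falciparum* and *P. vivax* episode counts will be analysed by negative binomial regression with log time at risk as offset, or by Poisson regression with child-level robust standard errors. Choose one, and say that it gives the primary rate ratio, confidence interval and p-value. Under section 11.3.2, apply the same rule to *P. malariae* and *P. ovale* counts. Plain Poisson can be kept as a sensitivity analysis. If a statistical analysis plan already says this, align the protocol wording with it.

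The cost is one sentence. STATA and SAS, both named in section 11.3.2, fit either model. The intervals will be wider if overdispersion is present, with some loss of apparent power. If it is absent, almost nothing is lost: with no heterogeneity the simulated rejection rates at 0.5 per child-year were 5.4% for both the Poisson and the robust test.
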